## Abstract

**Background:** Adolescence, when the most complex behaviors are refined to adult sophistication, represents a major window of opportunity and vulnerability for neuropsychological development. To support and protect this complex and active brain growth, different nutritional components considered essential need to be acquired from the diet. For instance, omega-3 fatty acids are mainly obtained from seafood, seeds, and walnuts. Known for their rich lipid profile, walnuts contain sizable amounts of an essential fatty acid, alpha-linolenic acid (ALA), the vegetable omega-3 fatty acid that is the precursor of two longer-chain omega-3 polyunsaturated fatty acids (omega-3 PUFA): docosahexaenoic (DHA) and eicosapentaenoic (EPA) acids. While there is growing evidence of neuropsychological improvements in the young developing brain associated with omega-3 PUFA intake, few studies have examined whether consuming walnuts during adolescence entails similar beneficial effects. There is a need to further explore the ways in which walnuts influence youthful brain function, particularly for the long-term. Thus, we designed the WALNUTs study (WSS), a population-based randomized controlled trial conducted in adolescents in Barcelona, Spain. We hypothesize that walnut intake will increase omega-3 PUFA tissue availability (particularly ALA) to a level that enhances the neuropsychological development during adolescence.

**Methodology/Design:** We conducted a 6-month population-based randomized controlled trial in teenagers (*n* = 800) and we aimed to determine the effectiveness of the intervention (four walnuts per day, or 30 kernel g, ~1.5g of ALA) in enhancing brain neuropsychological and socio-emotional development compared to a control group with no walnut intervention. Before randomization, different neuropsychological tests were recorded for all participants, and blood samples (in a subsample of participants) were collected to measure omega-3 PUFA levels at baseline, and all again, after randomization and the intervention. The data is now collected and we will conduct linear regression models to assess the effect of the intervention.

**Discussion:** The WALNUTs (WSS) study results will allow us to better understand the role of plant-based omega-3 PUFA intake from regular walnut consumption on neuropsychological development during adolescence. Results could be translated into nutritional public health recommendations targeting teenagers.

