Of all edible plants, walnuts are among the richest in the vegetable omega-3 fatty acid and alpha-linolenic acid (ALA), the precursor for DHA and EPA (12, 13). However, ALA is poorly transformed to EPA, while ALA itself has shown positive effects on brain function (14). Walnuts are also rich in fiber, vitamins, minerals, and other bioactive compounds capable of improving brain health (12). Short-term walnut consumption has been able to increase peripheral levels of EPA in humans (15), and different experimental studies have pointed to potential benefits in terms of cognition. Studies of walnut-fed rats fed showed improvements in working memory (12), and in humans, a parallel-group randomized controlled trial carried out among 447 older adults (mean age, 66.9 years) from Spain, found that a Mediterranean diet supplemented with 30g/day mixed nuts (including 15 g of raw, unprocessed walnuts) improved memory and delayed age-related cognitive decline (16).

Nut studies examining cognitive outcomes in young people are scarce. An observational cohort study assessed the association of various foods on the cognitive function of children and adolescents and reported a beneficial effect of nut consumption on visual attention and processing (17). One small double-blind, randomized, placebo-controlled crossover (8-week intervention and 6-week washout) trial with walnuts carried out with young college students aged 18 to 25 years showed improvements in inferential verbal reasoning (18). However, no experimental study focused on the effects of walnut consumption on adolescents' cognitive functions. Furthermore, a recent large observational study with NHANES data of 26,656 adult participants also found a protective association of walnut intake against depressive symptom scores (19).

In view of these preliminary findings, there is a need to further explore the potential brain development benefits of walnut consumption during adolescence, a period when the most complex behaviors are develop into adult sophistication. Moreover, adolescents represent a population that tends to be less targeted by health studies investigating the effects of environmental exposure on brain development (6). By conducting a population-based randomized controlled trial, the WALNUTs (WSS) study aims to assess whether walnut consumption has potential beneficial effects on teenage brain function using different neuropsychological and behavioral assessments.

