## Methods and Materials

### Trial Design

WALNUTs (WSS) is a multi-school, parallel (two-group), controlled, 6-month superiority randomized clinical trial in a large population-based sample aiming to include 800 healthy teenagers in Barcelona, Spain. After data collection, 771 participants were equally randomized in two groups (386/385), but because of some exclusions post-randomization, 748 were finally included. Study subjects were randomly assigned to two intervention groups just after baseline assessments: the walnut group (*n* = 370, consuming walnuts daily and advised to follow general healthful eating recommendations, such as eating a piece of fresh fruit every day) or control group (*n* = 378, not consuming walnuts and advised also to follow the same general healthful eating recommendations). They were assessed at baseline and after the intervention by several internationally validated neuropsychological tests and behavioral rating scales. Due to the project's budget limitations, a random subsample of 200 adolescents per group of intervention (*n* = 400) were targeted to measure changes in omega-3 PUFA biomarkers. We finally got 270 participants, 139 in the walnut group and 131 in the control group. All participants randomized to the walnut group received 30g/day of kernel walnuts to be incorporated into their diet for free. The type of walnuts selected, Californian walnuts, is estimated to contain about 9 g of ALA per 100 g (20, 21). There is evidence that young Spanish subjects between 10–13 and 14–17 years of age consume on average 5.7 g (SD 24.5 g) and 6.1 g (SD, 20.8 g) of nuts daily (22), which supports the feasibility of our trial design. Figure 1 shows the project's design and structure.

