## Data Analysis

Descriptive statistics (frequencies, means, standard deviations for normally distributed data; medians and interquartile ranges for nonparametric data) will be used to describe the baseline characteristics of the walnut and control groups. To assess the effect of the intervention on brain development, we use multivariable linear regression models. Similar regression models will be used to assess the effect of the intervention on red blood cell PUFA proportions, particularly ALA, as outcome variables. To assess the proportion of the effect of the intervention on brain development that is mediated by red blood cell PUFA changes, results will be compared in models with and without the mediator. All analyses will be based on the intention to treat in order to estimate the effectiveness of a public health recommendation (i.e., to encourage eating 30 g of walnuts per day). We also plan to conduct a per-protocol analysis with those who comply with the intervention, i.e., single days of reporting eating walnuts (≥ 100 days during 6 months) (34). The nominal statistical significance will be set at the *P* < 0.05 level (two-sided) for the primary outcomes. Statistical analyses are performed with STATA. A detailed statistical analysis plan will be established before database lock and any analyses.

Using multiple primary endpoints, the study will be considered successful if the results of either one of the primary endpoints is statistically significant in favor of the experimental treatment and/or treatment adherence. In this case, we will report for each primary endpoint a nominally significant level and the corrected *p*-value determined by the method for multiplicity adjustment.

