## Discussion

To the best of our knowledge, this is the first medium-term randomized intervention trial aiming to assess the effect of walnut consumption on adolescent brain development. The selected battery of neuropsychological and behavioral tests will provide the opportunity to enrich the interpretation of the findings. However, the design of this study is not exempt from potential limitations. First, the study selected walnuts for their richness in essential fatty acids, particularly ALA, with the hypothesis that they have an effect on the young developing brain. However, using walnuts will make the true PUFA content of the diet less consistent than if administered via a daily pill supplement. While the PUFA concentrations of California walnuts are fairly stable, we will minimize this potential bias by standardizing walnut dosage and type for the duration of the intervention. In any case, we measured the ALA biomarker in blood before and after the intervention as objective proof of adherence to the intervention. Second, performing a double-blind dietary trial, the gold standard of clinical trials, is problematic and known to be an important limitation in feeding studies of whole foods (35, 36). However, investigators performing biochemical determinations and statistical analyses are blinded to the intervention. Third, ensuring compliance of adolescents with daily walnut consumption for a period of 6 months is difficult and may result in lack of adherence and losses to follow-up. To offset this limitation, we planned to contact participants in the middle of the study, distribute recipes for dishes containing walnuts, ship walnuts to subjects' homes or schools for free, and ask the parent/tutor to supervise the intervention. In summary, this randomized feeding trial intends to focus on nutritional and neuropsychological sciences in the adolescents, a population group infrequently evaluated in clinical and public health research (https://www.nature.com/collections/vbmfnrsssw).

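### The planned with/without-mediator comparison does not identify omega-3's share of a walnut effect, because the red-cell PUFA marker may also track walnuts eaten

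*Protocol article*

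**What the plan says.** The Abstract hypothesises that "walnut intake will increase omega-3 PUFA tissue availability (particularly ALA) to a level that enhances the neuropsychological development during adolescence" and says the study "will allow us to better understand the role of plant-based omega-3 PUFA intake from regular walnut consumption". The randomised contrast is daily walnuts "compared to a control group with no walnut intervention".

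The Background states: "Walnuts are also rich in fiber, vitamins, minerals, and other bioactive compounds capable of improving brain health".

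Under Data Analysis, the article plans to estimate the proportion of the intervention effect "that is mediated by red blood cell PUFA changes", and gives the method: "results will be compared in models with and without the mediator". The Discussion says "we measured the ALA biomarker in blood before and after the intervention as objective proof of adherence to the intervention". Blood data are available for a subsample: "We finally got 270 participants, 139 in the walnut group and 131 in the control group".

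**The concern.** Two arms that differ by a whole food can show what offering that food does. They cannot show which of its components is responsible. The mediation analysis is the only step that could tie an effect to omega-3, and its mediator includes a fatty acid that the article itself uses to show that walnuts were eaten. A marker of walnuts eaten is also a marker of the fibre, vitamins, minerals and other bioactive compounds eaten with them.

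Within the walnut arm, how much is eaten is each teenager's own behaviour, not the result of randomisation. When the marker enters the model, its coefficient can therefore pick up any benefit that rises with intake, whichever component causes it, and any trait of teenagers who adhere well. At stake is the mechanism: a sizeable mediated share could be read as support for the omega-3 hypothesis when the data would look the same without any omega-3 effect.

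**Working it through.** The article gives no mediated share, so there is no stated figure to reproduce. The check asks what the planned comparison returns when the truth is known.

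**Inputs.** From the article: two arms, whole walnuts against none; outcome regressed on arm, with and without red-cell PUFA change; 139 and 131 participants with blood data. Assumed, because the article gives no figure: intake explains a share *s* = 20%, 50% or 80% of PUFA variance in the walnut arm; the rest of the PUFA variance is the same in both arms; the arms are of equal size.

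**Case 1: omega-3 does nothing.** Let *D* be walnuts eaten (0 in controls), outcome = *bD* + error, PUFA change = *kD* + *e*.
- Total effect (model without the mediator) = *b* × mean(*D*).
- PUFA coefficient (model with the mediator) = 0.5·*bk*·Var(*D*) / [0.5·*k*²·Var(*D*) + Var(*e*)].
- Apparent share = 0.5·*k*²·Var(*D*) / [0.5·*k*²·Var(*D*) + Var(*e*)] = *s* / (2 − *s*).
- *s* = 0.2: 0.2/1.8 = 11.1%. *s* = 0.5: 0.5/1.5 = 33.3%. *s* = 0.8: 0.8/1.2 = 66.7%. The true share is 0% each time. Simulation with 400,000 per arm gave 11%, 33% and 67%.

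**Case 2: omega-3 does everything, but the marker is noisy.** Let the outcome depend only on tissue omega-3, and let a fraction *f* of the non-intake marker variance be measurement error. The true share is 100%. The apparent share is the marker's pooled within-arm reliability: [*s*/2 + (1 − *s*)(1 − *f*)] / [*s*/2 + (1 − *s*)].
- *s* = 0.2, *f* = 0.75: (0.10 + 0.20)/0.90 = 33%.
- *s* = 0.5, *f* = 0.50: (0.25 + 0.25)/0.75 = 67%.
- *s* = 0.8, *f* = 0.50: (0.40 + 0.10)/0.60 = 83%.

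So an observed share of 33% or 67% fits a truth of 0% and a truth of 100%, depending on quantities that the trial does not fix.

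**Does sample size matter?** A separate simulation used 139 and 131 participants, a fraction of walnuts eaten centred on 0.5 (SD 0.3, limited to 0–1), a total effect of 3 units, outcome SD 15, and marker noise SD of 0.01, 0.15, 0.3 and 0.6 (all but the arm sizes, 3 units and SD 15 are assumptions). With no omega-3 effect the comparison showed 101%, 63%, 29% and 9% mediated. With omega-3 causing everything in proportion to dose it showed 96%, 62%, 29% and 10%. The two rows agree by construction, because every component arrives in a fixed ratio to walnuts eaten. At 5,000 per arm the no-omega-3 case gave 98%, 64%, 30% and 9%, so a larger blood sample would not remove the problem.

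**Would adding reported walnut days cure it?** No. If reported days carry an error SD of half the true SD of intake (assumed), their reliability is 1/(1 + 0.25) = 0.8. In Case 1, adding days alone then leaves 1 − 0.8 = 20% of the total effect on the arm term (3.0 units falls to 0.6), because the variable is largely a restatement of arm. In Case 2 it moves the estimate further from the truth: in simulation, 33% became about 27% (*s* = 0.2, *f* = 0.75) and 83% became about 64% (*s* = 0.8, *f* = 0.50), with the share computed as a product of coefficients.

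**The case against.** The strongest reply has four parts.

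- **The article claims less than proof.** A reader might infer that the trial undertakes to demonstrate omega-3's role. The Abstract speaks only of better understanding, the last paragraph of the Background keeps the neuropsychological and the PUFA hypotheses apart, and Data Analysis frames the main analysis as the effectiveness of a recommendation to eat walnuts. This stands. What remains is the Abstract's mechanistic hypothesis and a planned numerical share attributed to PUFA.
- **The mediator is not ALA alone.** It is red-cell PUFA changes. In Data Analysis the emphasis on ALA belongs to the sentence on PUFA as outcomes, and only ALA is named as proof of adherence. The article also gives seafood as a PUFA source and says ALA converts poorly to EPA, so a composite marker or one of the other PUFAs may follow walnuts only loosely. This stands, and it points towards the lower end of the range.
- **The bias need not run upward.** A reader might infer that the comparison always credits omega-3 with other components' effects. Case 2 shows that it can also understate a real omega-3 effect. This stands.
- **The analysis plan is not shown.** Covariates and sensitivity analyses may well be in it, and their absence here is no fault. But the comparison, the marker's second role and the omega-3 conclusion are stated in the article, and no choice of covariates creates a contrast that separates omega-3 from the rest of the walnut.

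**Conclusion.** The point holds in a limited form. The with/without difference does not identify omega-3's share of any walnut effect. With no omega-3 effect at all it returns about 11% to 67% under the assumed 20% to 80% intake share of walnut-arm PUFA variance. With a wholly omega-3 effect it can return 33% to 83% under the assumed marker error. The sizes rest entirely on these assumptions. That a non-zero share appears without any omega-3 effect needs only that the marker tracks intake, which the Discussion asserts for ALA, and that some benefit rises with walnuts eaten, which the Background makes plausible.

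A reader might go further and doubt the trial's main result. The article does not support that: the intention-to-treat effect of offering walnuts rests on randomisation and is unaffected. Only the attribution to omega-3 is in question.

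**What to change.** 1. **Abstract, Discussion paragraph.** State the conclusion as the effect of offering 30 g of walnuts a day, and say that the two-arm design does not isolate omega-3 from other walnut components. The limitations in the main Discussion cover PUFA content, blinding and compliance, so the same sentence belongs there.
2. **Data Analysis.** Label the mediation analysis exploratory. Adjust it for baseline PUFA and the baseline outcome score. Report a sensitivity analysis for unmeasured mediator–outcome confounding and for marker error. Do not report the simple with/without difference as omega-3's share.
3. **Do not rely on reported walnut days as the correction.** Only the walnut group reported them, they are nearly collinear with arm, and they lower the estimate further when omega-3 is the true mediator.

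The baseline adjustment does not make the share identifiable; the wording and the label do the main work. The article says a detailed analysis plan is to be set before database lock, so the change can be made there. It needs no new data. The price is a weaker omega-3 claim and a little more analysis.

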**Trial Registration:**
ClinicalTrials.gov, U.S. National Library of Medicine, National Institutes of Health # NCT02590848. Retrospectively registered 29/10/2015.

## Background

Adolescence is a critical period for brain development, mainly because the prefrontal cortex, which is responsible for important functions such as logical thinking, working memory, and organizing skills, is the last region of the brain to mature around the early twenties (1). Adolescence is also a time of refinement of brain connectivity and complex behaviors. Indeed, it is a critical period for the development of psychological and psychiatric pathologies, such as substance abuse, schizophrenia, and mood and anxiety disorders (1–3).

The brain is a highly active organ and its development and metabolism require a large amount of energy and nutrients (4, 5). In this context, lack of essential nutrients may interfere with brain development in youth. Therefore, enhancing these complex processes, such as by adopting a healthy and balanced diet providing essential nutrients, may have long-term functional consequences (6).

Making up ~15 to 30% of the brain's dry weight (7), PUFAs are an example of essential and semi-essential nutritional components that are mostly obtained through the diet (mainly from seafood, seeds, and walnuts) (8). Three of these PUFAs play an essential role in brain development: long-chain omega-3 acids—docosahexaenoic acid (DHA) and eicosapentaenoic acid (EPA)—and the omega-6 acid arachidonic acid (AA). Experimental and clinical studies have demonstrated the importance of PUFAs in the function and architecture of the central nervous system throughout various stages of life, from neural development to neurodegeneration (4, 7). In the adolescent population, several large randomized controlled trials of supplementation with DHA and EPA have reported a favorable effect on neuropsychological and behavioral outcomes (9, 10). Thus, a large randomized controlled trial conducted in healthy young adults using computerized cognitive tests found that reaction time latencies and working memory were improved after 6 months of DHA supplementation (11).

Of all edible plants, walnuts are among the richest in the vegetable omega-3 fatty acid and alpha-linolenic acid (ALA), the precursor for DHA and EPA (12, 13). However, ALA is poorly transformed to EPA, while ALA itself has shown positive effects on brain function (14). Walnuts are also rich in fiber, vitamins, minerals, and other bioactive compounds capable of improving brain health (12). Short-term walnut consumption has been able to increase peripheral levels of EPA in humans (15), and different experimental studies have pointed to potential benefits in terms of cognition. Studies of walnut-fed rats fed showed improvements in working memory (12), and in humans, a parallel-group randomized controlled trial carried out among 447 older adults (mean age, 66.9 years) from Spain, found that a Mediterranean diet supplemented with 30g/day mixed nuts (including 15 g of raw, unprocessed walnuts) improved memory and delayed age-related cognitive decline (16).

Nut studies examining cognitive outcomes in young people are scarce. An observational cohort study assessed the association of various foods on the cognitive function of children and adolescents and reported a beneficial effect of nut consumption on visual attention and processing (17). One small double-blind, randomized, placebo-controlled crossover (8-week intervention and 6-week washout) trial with walnuts carried out with young college students aged 18 to 25 years showed improvements in inferential verbal reasoning (18). However, no experimental study focused on the effects of walnut consumption on adolescents' cognitive functions. Furthermore, a recent large observational study with NHANES data of 26,656 adult participants also found a protective association of walnut intake against depressive symptom scores (19).

In view of these preliminary findings, there is a need to further explore the potential brain development benefits of walnut consumption during adolescence, a period when the most complex behaviors are develop into adult sophistication. Moreover, adolescents represent a population that tends to be less targeted by health studies investigating the effects of environmental exposure on brain development (6). By conducting a population-based randomized controlled trial, the WALNUTs (WSS) study aims to assess whether walnut consumption has potential beneficial effects on teenage brain function using different neuropsychological and behavioral assessments.

We hypothesized that walnut supplementation for 6 months would enhance neuropsychological and behavioral (socio-emotional) development among healthy teenagers. We further hypothesized that a walnut intervention for 6 months would increase omega-3 PUFA tissue availability.

